#### Reimbursement

Patients who participate and complete the 1-month survey will be reimbursed US$25 whether or not they consent to participate in the clinical trial. Study staff will reimburse patients who consent to participating in the clinical trial and completing the extended 1-month survey with an additional US$25. All reimbursements will be via reloadable debit cards. The debit cards utilize the MasterCard payment system and are accepted at virtually every institution that accepts a credit card. Participants will also be reimbursed US$25 for the 6-month follow-up survey and US$50 for each salivary cotinine sample returned.

### Project measures (Table 3)

#### Tobacco abstinence

Outcome measures are adapted from the Society for Research on Nicotine and Tobacco’s Workgroup on Abstinence Measures and Workgroup on Biochemical Verification [29, 30]. Our primary endpoint is 7-day, verified cigarette abstinence at 1 month after enrollment. Subjects with missing data will be counted as smokers.

#### Verification of abstinence

We will use either mailed salivary cotinine or in-person carbon monoxide (CO) testing to confirm smoking status. Participants who report 7-day point-prevalence abstinence, and who are not taking NRT, will be asked to provide a saliva sample. Cotinine is the measure of choice because of its sensitivity and specificity [30]. Samples will be stored in a − 20 °C freezer until laboratory analysis. Participants who are still using NRT, or who refuse salivary cotinine, will be verified via CO testing. Those with < 10 ppm will be considered abstinent.

#### Secondary outcomes, mediators, and moderators

Study counselors will track counseling data, which will be summarized as “total counseling time” for analyses. We will assess the type, the dose, and the number of days of medication was used via the method of Williams et al. [31, 32]. This will be summarized as “number of days of medication use” for analyses. Default-related variables are derived from the academic literature on choice theory and include smokers’ perceptions of provider attitudes toward tobacco-cessation treatment (implied recommendation), smokers perceptions of the degree to which their provider recommends tobacco-cessation treatment (implied recommendation), perceptions of the “status quo” for hospital tobacco-cessation treatment (status quo bias), and perceptions of paternalistic treatment by UKanQuit staff [13, 23, 33].

#### Intervention costs

We will prospectively track variable intervention costs. Costs will include inpatient counselor services, post-discharge counseling time, and initial pharmacotherapy dispensed at baseline. During the 6-month follow-up call, we will ask participants to recall their use of pharmacotherapy after the initial supply. Personnel time will be valued at Bureau of Labor Statistics (www.bls.gov) wages plus benefits for an appropriately trained health-promotion professional. Pharmacotherapy costs will be based upon retail prices estimated from on-line pharmacy websites. Intervention costs will be tracked as they are incurred. We will exclude research costs. We will not discount either costs or benefits.

#### Fidelity monitoring

Fidelity to the study protocol will be assessed by in-person fidelity assessments during hospital consults. To assess the quality of the intervention and control conditions, we will assess the degree to which study staff accurately: (1) provide brief advice and (2) perform the appropriate intervention for OPT OUT versus OPT IN. Data on fidelity will be entered into a RedCAP database and reported back to study staff to encourage adherence to protocols.

#### Protection against risks

There are minimal risks in this study. Any emails used to transmit study participant information will be encrypted to protect the privacy of patients. Salivary cotinine samples are noninvasive; samples will be labeled with participants’ study ID numbers, rather than names, to protect participants’ privacy. When collecting proxy verification of smoking status, no information about the patients’ participation in the trial will be provided to the proxy besides the participants’ name and the fact that they had nominated the proxy to provide verification of smoking status at the end of a health-promotion study.

Standard language in our consent procedure assures the participants of the confidential nature of the study. Those who elect to participate will be clearly told that they may withdraw from the study at any time without jeopardizing current or future care at any medical facility. Potential participants will also be informed of alternative treatments (i.e., using other smoking-cessation programs, purchasing nicotine gum, patches, or lozenges from the pharmacy, obtaining a prescription for a nicotine inhaler, nasal spray, or other smoking-cessation products from their physician). These standards are strictly adhered to and monitored by the KUMC Institutional Review Board. Only summaries of group data will be reported in any publications or presentations, with no identification of individuals. All records will be kept in locked filing cabinets in offices that are kept locked when unoccupied. Subject files will be kept in a secure area, with access only by designated staff members (PI and co-investigators).

### Data management

Data management will follow procedures developed for Enhancing Quitline Utilization among In-Patients (EQUIP). UKanQuit service data, and survey data collected by research assistants, will be directly entered via tablet into REDCap. The project director will coordinate data retrieval from the EHR. The data manager will conduct initial data cleaning, identifying and tagging any crossovers, conversion into proper format for data analysis, and recoding using standard operating procedures. All data will be imported into SAS for study analyses. Cleaning and management routines (e.g., conversion of birth dates to ages, logical checks for continuous variables, compliance with skip patterns, missing data codes) will be conducted using SAS.

### Data safety and monitoring plan

Due to the low level of risks involved in the proposed study, a Data and Safety Monitoring Board (DSMB) will not be necessary. The data and safety monitoring will be overseen by the PI, [name], and an annual progress report will be provided to the Human Subjects Committee of the University of Kansas Medical Center as well as the NIH. The purpose of this data and safety monitoring plan is to ensure the safety of study participants and the validity of data in compliance with National Institutes of Health (NIH) requirement of Data and Safety Monitoring for Clinical Trials. This section outlines essential elements of the Data Safety and Monitoring (DSM) plan for this clinical trial.

#### Plans for assuring data accuracy and protocol compliance

Data management activities for this project will encompass data entry, data cleaning, identifying and tagging any crossovers, conversion into proper format for data analysis and recoding. In addition, a computer-based tracking system will be developed to follow each patient and to prompt the staff for the upcoming data collection point. Data collection points for each subject will be calculated from their initial date of contact. Data entry will be performed on site under direction of the PI and the study statistician. Keypunching routines will adhere to the codebook specifications written by the team. Codebooks will include variable formats (numeric/alpha), min/max ranges and any skip patterns. Data will be double entered utilizing two separate databases and data entry personnel for the two databases would be different. Both the databases and the tracking system would be password protected for security and maintenance of confidentiality. At the end of each data entry period, data would be backed up onto a storage unit. Checks built into the database will ensure that individuals not meeting eligibility criteria are flagged and excluded from data analysis.

#### Data sharing

This study will generate quantitative and qualitative data from the randomized trial. The final quantitative dataset will include self-reported demographic and behavioral data from subjects. Because we collect data at multiple time points from participants over the 6-month period that each participant will be in the study, we will collect identifying information. Prior to data sharing, we will remove or convert all identifying information (date of birth will be converted to age, date of admission and discharge will be removed, and other identifiers will be removed). There may remain the possibility of deductive disclosure of subjects with unusual characteristics. Thus, we will make the data and associated documentation available to users under a data-sharing agreement that provides for: (1) a commitment to using the data only for research purposes and not to identify any individual participant, (2) a commitment to securing the data using appropriate computer technology, and (3) a commitment to destroying or returning the data after analyses are completed. Data will be saved as SAS or SPSS files, saved to disk, and mailed to users.

## Data analysis

### Overview of hypotheses and analyses

**Table 4 Tab4:** Virtual response patterns for quit rate endpoint

	OPT IN	OPT OUT	
		Efficacy	
No differences	15.7%	15.7%	Both have equal quit rates
Small but unlikely	15.7%	20.0%	OPT OUT is moderately better
Expected	15.7%	25.2%	OPT OUT is better at expected differences

The overall design is a randomized controlled trial (RCT) with individual assignment to groups. Bayesian analysis will drive participant allocation. Prior to outcome analyses we will examine baseline data to evaluate if randomization achieved equivalent groups. In addition, we will conduct process, outcome, mediation, and cost analyses.

#### Bayesian design

We will perform a prospective randomized comparative effectiveness *Bayesian adaptive design study* [34]. Our endpoint is the percentage of patients with verified cessation at 1 month (4 weeks) post randomization. We will perform our first planned interim analyses when we have endpoint data on 400 patients. The arm that appears to be performing the best will get more participants allocated to it in the subsequent randomization period. A new adaptive randomization structure will be updated every 13 weeks, using up-to-date outcome data, until the trial meets success or all 1000 subjects are consented. The main outcome analysis will use an ITT approach, with the denominator being all participants randomized to the study. Data from patients we are unable to reach at 1 month will be de-identified and included in data analyses.

For this study the primary endpoint is modeled:
*S*
_*QjT*_|*n*
_*jT*_ ~ Bino(*n*
_*jT*_
*,θ*
^*Q*^
_*j*_) quitting.

In addition, we provide “weakly informative” priors:logit(*θ*
^*Q*^
_*j*_) ~ N(0,100^2^).

Using the endpoint data and the prior probabilities, we then use Markov Chain Monte Carlo computations to obtain the Bayesian posterior distributions for the endpoint (i.e., quitting). We will stop randomizing into the comparative trial if the probability of a study arm having maximum utility is greater than 0.9925. The arm having the maximum quit rate is *M*
_*T*_ = max(*θ*
^*Q*^
_*1,*_
*θ*
^*Q*^
_*2*_). The stopping rule is mathematically *P*(*M*
_*T*_ > .9925). If a maximum arm is not identified after 500 patients, this procedure and accrual will continue until a maximum arm is identified or we enroll all 1000 patients. It is possible that we will reach the maximum utility criterion before 1000 patients are consented. Should this occur, we will stop the trial and begin outcome, cost, and mediation analyses in order to quickly disseminate findings.

After the maximum arm probability is evaluated, the next round of patients is randomized using a formula that favors the arm with the maximum quit rate, thus taking advantage of the information gained from our interim analyses. Using this formula, each arm is allocated for the next patients to be enrolled in the *j*
^th^ arm proportional to:$$ {V^{\ast}}_j=\mathrm{sqrt}\Big(\Pr \left({M}_{jT}={\theta^Q}_1\Big)\mathrm{Var}\left({\theta^Q}_1\right)/\left({n}_{jT}+1\right)\right). $$

This type of allocation has more desirable properties than simply using Pr(*M*
_*jT*_ = *θ*
^*Q*^
_*1*_). In other words, using this approach will allow us to assign more patients to the most promising arm, and fewer patients to the least. Regardless of when the maximum arm probability cut point is reached, we will confirm this finding with a subsequent analysis and evaluation (> .99) after all data from all enrolled patients are obtained, as some will be in the study when early success criteria are identified.

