#### Power, sample size, and trial duration

In accordance with guidelines for adaptive design power analyses [34], we used simulated data to determine the power, sample size, and anticipated duration of the study. We created virtual responses for our “expected” quit rates, another for “small but unlikely” quit rates, and a third for “no differences” in quit rates. We performed three sets of trial simulations (Table 4). Each set involved many trial simulations that identified power (the probability of success) in two scenarios—one for early success (i.e., being able to stop randomization early) and one for late success (i.e., upon enrolling all 1000 patients). While two of these combinations are very unlikely to occur, we included all scenarios. First, under the “expected” quit rates, we estimated (identified) that 92% of the simulated trials had early success, 3% late success, and only 5% had incomplete results. Thus, this scenario had 95% power. The average sample size of this trial scenario was 625 patients with more than half (387) in the better OPT-OUT arm. The average length of these simulated trials was 98 weeks. Second, if there are “small but unlikely” quit rates, we identified that 30% of the simulated trials had early success, 5% had late success, and 65% had incomplete results. This trial scenario had 35% power and the sample size of this trial scenario was on average 903 with more than half (530) in the better OPT-OUT arm. The average length of this trial scenario was 142 weeks. Third, we examined the scenario that serves as our null hypothesis. In this scenario there are no differences in quit rates among the arms. The extent to which this scenario is “successful” reflects our Type-I error rate. For this scenario, we identified that 4% of the simulated trials had early success, 1% late success. This trial scenario produced an appropriate expected Type-I error (*α* = .05). The sample size of this scenario on average was 986 patients, with about half (495) in the OPT-OUT arm. The average length of the trials under this scenario was 155 weeks—approximately 3 years of recruitment. Hence, our maximal sample size of 1000, in 3 years of recruitment, provides ample time and participants to identify project outcomes under all three scenarios.

**Table 5 Tab5:** Study hypotheses, measures, and analytic strategy

Purpose	Variables	Analytic strategy

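### Both operative formulas in the Bayesian design section are wrong as printed: the allocation weight ignores which arm is better, and the stopping formula tests for a quit rate above 99.25%

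*Protocol article*

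**What the plan says.** All of this is in the protocol article, mainly under Data analysis, Bayesian design.

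**Allocation.** In words, after each evaluation "the next round of patients is randomized using a formula that favors the arm with the maximum quit rate". The end of that section and the Discussion (Research contribution) repeat the aim. The formula printed for the weight of arm j, without the superscript Q, is

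`V*_j = sqrt( Pr(M_jT = theta_1) * Var(theta_1) / (n_jT + 1) )`

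The index j stands on V, M and n; both theta terms carry the index 1. The next sentence, which compares this rule with a simpler one, again uses Pr(M_jT = theta_1).

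**Stopping.** In words: "We will stop randomizing into the comparative trial if the probability of a study arm having maximum utility is greater than 0.9925". The article then defines M_T = max(theta_1, theta_2) and continues "The stopping rule is mathematically" P(M_T > .9925).

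**Simulated results** (Power, sample size, and trial duration). For the expected quit rates: "The average sample size of this trial scenario was 625 patients with more than half (387) in the better OPT-OUT arm", with 92% early success. For the small difference, 530 of 903 were in OPT OUT; for no difference, 495 of 986.

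**The concern.** In each case the sentence and the formula beside it state different rules. A weight meant to send patients to the better arm contains nothing that reflects the quit rate of arm j. A rule described as a probability of being best is written as a statement about the size of a quit rate.

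These are decision rules, not background. Under Enrollment and random allocation, the study biostatistician may change the ratio in accordance with this design. The article states that there is no DSMB, so no such board would check the rules. Recruitment had already begun when the article was submitted. Anyone who programs or audits the adaptive steps from the formulas would get a procedure that differs from the one described.

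**Working it through.** **Inputs.** Planning quit rates are 15.7% (OPT IN) and 25.2% (OPT OUT), from Projected quit rates. The two formulas and the definition of M_T are from Bayesian design. The simulated allocations are from Power, sample size, and trial duration.

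**1. The article's own shares in OPT OUT.**
- Expected: 387/625 = 61.9%
- Small difference: 530/903 = 58.7%
- No difference: 495/986 = 50.2%

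The share moves above one half only when OPT OUT is truly better, so the simulated rule responded to outcomes.

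**2. The printed allocation weight.** M_jT is undefined; take it as M_T, the only maximum that is defined. Then Pr(M_T = theta_1) and Var(theta_1) are the same number for both arms and cancel:

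`V*_1 / V*_2 = sqrt( (n_2 + 1) / (n_1 + 1) )`

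Outcomes drop out, and the larger arm gets the smaller share. Two worked cases, with arm 1 = OPT IN, arm 2 = OPT OUT and share to OPT OUT = V_2/(V_1 + V_2):

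- *200 v 200 patients, 31 v 50 quitters.* Pr(OPT OUT best) = 0.9907; the variances are 0.000652 and 0.000933. Printed: equal n, share 0.500. Arm-indexed: V_2/V_1 = sqrt[(0.99065 × 0.000933)/(0.00935 × 0.000652)] = 12.3, share 12.3/13.3 = 0.925.
- *190 v 230 patients, 31 v 46 quitters.* Pr(OPT OUT best) = 0.8345. Printed: sqrt(191)/(sqrt(191) + sqrt(231)) = 13.82/29.02 = 0.476, so fewer than half go to the arm that is ahead. Arm-indexed: 0.668.

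**3. The allocation rule over whole trials.** Simulation with 4,000 trials per scenario: 6.7 patients per week, 4-week endpoint delay, 1:1 until 400 endpoints, looks every 13 weeks, maximum 1000, and stopping as worded (probability of being best > 0.9925). The article does not say from what size success may be declared, so both 400 and 500 were run. Entries are the mean number in OPT OUT of the mean total, expected scenario.

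| Weight | Success from 400 | Success from 500 |
|---|---|---|
| Arm-indexed | 356 of 605 (59%) | 403 of 654 (62%) |
| As printed | 293 of 586 (50%) | 320 of 640 (50%) |

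In the small-difference scenario the arm-indexed weight gives about 60% and the printed weight 50%. The article's 62% and 59% fit the first and not the second.

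The match is not exact. The stated 625 lies between 605 and 654, and the arm-indexed total success is 90 to 91% against the stated 95% (the printed weight gives 93 to 94%). The article's simulation settings are not fully stated, and the point does not rest on that gap.

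**4. The printed stopping formula.** M_T is a quit rate, so P(M_T > .9925) is the probability that the larger quit rate exceeds 99.25%. No value is given that this probability must reach. With 50 quitters among 200, the posterior probability that the rate exceeds 0.9925 is about 1e-272. Read literally, early stopping would be 0%, against the 92% reported.

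**The case against.** The strongest reply is that the intent is plain. Both rules are stated correctly in words beside the formulas and again in the Discussion. The reported shares of 62% and 59% and the 92% early success could not have come from the printed formulas. On this view there is a wrong subscript and a misplaced bracket in a journal article that condenses a fuller protocol, and nothing shows that anyone programs from the article. This stands as to consequence. It does not remove the contradiction: the article chose to print the operative rules, and theta_1 appears twice in the formula and again in the following sentence, while the binomial model and the prior in the same section correctly carry theta_j.

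A second reply is that the cancellation depends on how M_jT is read. If Pr(M_jT = theta_1) were taken to mean the probability that arm j is best, the rule would favor the better arm. In the 200 v 200 case the ratio would be sqrt(0.99065/0.00935) = 10.3 and the share 10.3/11.3 = 0.91. That reading needs a definition the article does not give, and it still uses arm 1's variance for both arms.

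A reader might also infer that the sample sizes conflict, because "We will perform our first planned interim analyses when we have endpoint data on 400 patients" is followed by "If a maximum arm is not identified after 500 patients, this procedure and accrual will continue", and 625 - 387 = 238 OPT IN patients is below the 250 that 1:1 allocation up to 500 would give. The article does not support this. It nowhere says that 1:1 allocation runs to 500. At 6.7 per week with a 4-week delay, about 400 + 26.8 = 427 patients are enrolled at the first look and about 427 + 87.1 = 514 at the next. Some 213 per arm at the first look leaves room for an average of 238. The role of 500 could be clearer, but there is no contradiction.

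**Conclusion.** Both formulas are wrong as printed and must be corrected. The allocation weight, with M_jT read as M_T, gives about 50% in OPT OUT where the article reports 59% to 62%. The stopping formula could never be met at the planning rates, although the sentence before it gives a usable rule.

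A reader might infer that the trial was designed, simulated or coded without adaptation or early stopping, and that its stated operating characteristics are void. The article does not support that: its wording and its reported results indicate that the intended rules were simulated, and the randomization code is not shown.

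Nor should the two effects be added together. The 50% splits in the table use the stopping rule as worded. Under the printed stopping formula every trial would instead run to 1000, and with 500 per arm the final check at > .99 would still succeed in about 92% of trials at the expected rates. What that formula would remove is early stopping, not the trial's power.

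The algebra rests only on the printed text and on reading M_jT as M_T. The simulated shares rest also on the settings listed and on a normal approximation to the posterior on the logit scale with a near-flat prior.

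**What to change.** In the Bayesian design section:

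- Print the allocation weight as `V*_j = sqrt( Pr(theta_j = M_T | data) * Var(theta_j | data) / (n_jT + 1) )`, state that arm j receives the share V*_j divided by the sum over arms, and correct the index in the following sentence. Replace M_jT by M_T.
- Print the stopping rule as: stop if the maximum over j of `Pr(theta_j = M_T | data)` exceeds 0.9925.
- Check the randomization and interim-analysis code against these two lines, and record that the reported simulations used them.

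The cost is a correction to the text and a code check. No patients, visits or data are added. If the code already follows the worded rules, the design and its stated operating characteristics need no change on this account.
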